## **MAIN OUTCOMES**

### ***Variables***

#### ***Primary***

Development of persistent microalbuminuria (i.e. urinary albumin excretion rate  $>20$   $\mu\text{g}/\text{min}$  in at least 2 of 3 consecutive overnight urine collections confirmed in two consecutive visits). Whenever a patient will be found to have 2 of 3 collections in the microalbuminuric range, he will be asked to submit 3 additional consecutive collections within 2 months. If urinary albumin excretion rate is still  $>20$   $\mu\text{g}/\text{min}$  in at least 2 of 3 samples, he will be considered to be microalbuminuric and to have reached the end point.

### *Secondary*

- Regression to low-normal albuminuria (i.e. urinary albumin excretion rate  $<7 \mu\text{g}/\text{min}$  in at least 2 of 3 consecutive overnight urine collections confirmed in two consecutive visits);
- Albuminuria (considered as a continuous variable);
- Serum creatinine (versus baseline);
- Incidence of fatal and non-fatal cardiovascular events (stroke, acute myocardial infarction, sudden death)

### *Safety variables*

They will include serious and non-serious adverse events and any clinical or laboratory abnormality (such as acute hypotension, cough, acute renal function deterioration or hyperkalemia) possibly related to the study drugs.

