Glycated hemoglobin, lipids, the glomerular filtration rate (GFR, in a subgroup), and routine clinical and laboratory parameters will be evaluated at randomization, 3 and 6 months after randomization and every 6 months up to study end. The measurements of albuminuria (by nephelometry) and GFR [by iohexol plasma clearance (21)] will be centralized at the laboratory of our Clinical Research Center. This laboratory already served for centralized measurements of GFR [by a technique that has been set up by the head of the laboratory (21)] in previous multicenter, randomized trials in non-diabetic renal disease (22-24) and for all routine laboratory tests including albuminuria, lipids, hematochemistry, blood cell counts in a previous large scale, multicenter, randomized trial in patients with type 2 diabetes (14), as well as in other ongoing clinical trials in a similar typology of patients. All the investigators involved in laboratory measurements will be blinded to the treatment assignments of the subjects.

All clinical and laboratory parameters as well as any serious and non serious adverse event will be recorded throughout the study for safety analyses.

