## **DATA MANAGEMENT**

In order to ensure that the data base accurately reflects data of the case report forms, a double entry procedure will be used.

The data entry will be made by the staff of the Mario Negri Institute Drug Monitoring Unit. Data will be entered by different staff members in the same data base. Inconsistencies derived from a computer-assisted comparison of these two data entries will be carefully clarified. In addition, a systematic and extensive electronic validation of the quality of the data base will take place.

Pre- and concomitant medication, concurrent diseases as well as adverse events will be coded according to standardized dictionaries. Once all data discrepancies will be corrected, the database will be locked and data converted into SAS-transport files. Due to the PROBE design of the study, only those assessing the outcomes will be blinded to group assignment.

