## **ADVERSE EVENT DEFINITION**

### Adverse Event

Any untoward medical occurrence in a patient or clinical investigation subject administered a pharmaceutical product and which does not necessarily have to have a causal relationship with this treatment.

An adverse event (AE) can therefore be any unfavourable and unintended sign (including an abnormal laboratory finding, for example), symptom, or disease temporally associated with the use of a medicinal product, whether or not considered related to the medicinal product.

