#### **COLLECTION/REGISTRATION OF INFORMATION**

Adverse events will be monitored at each visit and by telephone reports from responsible caregivers as needed between outpatient visits.

Any adverse event reported spontaneously or upon questioning will be evaluated by the Investigator and recorded on the relevant page in the case report form.

However, if the event includes a group of signs and symptoms, which, when considered together, are known or presumed to characterize a syndrome, only one form must be filled in. In this case, all events will be fully described, but any additional information such as intensity, outcome, causality, etc., will refer to the syndrome only. For each adverse event the Investigator is required to evaluate the nature of the event, the date and time of its onset (if known), the date and time the adverse event stopped (if known), the duration of the event and its maximum intensity. The Investigator will record any remedial action taken and the final outcome of the adverse event. All modern facilities for resuscitation must be immediately available in case of emergency. The Investigator is also required to assess the causal relationship between the event and the study treatment.

All the patients experiencing adverse events must be monitored until symptoms and any abnormal laboratory values have returned to baseline, or until there is a satisfactory explanation for the changes observed, or until death, in which case a full pathologist's report should be supplied, if possible. All findings must be recorded on the "adverse event" page in the case report forms and in the patients' medical records.

In case of serious adverse events, the following reporting procedure has to be followed: for all serious adverse events which occur during the study whether considered to be associated with the trial drug or not, the Investigator must send the initial SAE report immediately (within 24 hours from the knowledge of the event),

by fax to Mario Negri Institute; the investigator has to document the event also on an “adverse event” page in the case report forms.

If necessary, one or more follow-up reports including all additional information obtained on the serious adverse event must be prepared by the Investigator.

The contact addresses for reporting of serious adverse events is:

[name], *Clinical Monitor*

Drug Monitoring Unit

Istituto di Ricerche Farmacologiche Mario Negri

Centro di Ricerche Cliniche per le Malattie Rare

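### The Safety variables section adds hyperkalemia and other abnormalities only if judged possibly drug-related; in an open-label trial this partly exposes the safety comparison, mainly for potassium

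*Protocol*

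**What the plan says.** The Protocol's Safety variables section (under Main Outcomes) is one sentence with two parts. The first part has no causality condition: "They will include serious and non-serious adverse events". The second part does: "any clinical or laboratory abnormality (such as acute hypotension, cough, acute renal function deterioration or hyperkalemia) possibly related to the study drugs".

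Other sections of the Protocol bear on how this is read:

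- **Study Design and Treatment:** "All clinical and laboratory parameters as well as any serious and non serious adverse event will be recorded throughout the study for safety analyses". No relatedness condition appears there.
- **Adverse Event (definition):** an adverse event is an occurrence "which does not necessarily have to have a causal relationship with this treatment". It can be an "unfavourable and unintended sign (including an abnormal laboratory finding, for example"), and it counts when "temporally associated with the use of a medicinal product, whether or not considered related to the medicinal product".
- **Collection/Registration of Information:** "The Investigator is also required to assess the causal relationship between the event and the study treatment".
- **Data Management:** under the open-label design, "only those assessing the outcomes will be blinded to group assignment".
- **Centers:** the End Point Committee reviews primary and secondary end points blindly. Safety variables are not in its stated remit.
- **Secondary outcomes:** serum creatinine against baseline is listed. Potassium is not.
- **Appendix 1, footnotes 3 and 4:** potassium and creatinine belong to both the complete and the selected blood examinations, so they are measured on a fixed schedule in every arm.

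**The concern.** Hyperkalemia and acute renal function deterioration are harms that the Protocol itself names for these drugs. How often they occur under dual as against single blockade is part of deciding whether any benefit of the combination is worth having. The sentence that defines the safety variables admits these abnormalities on a judgement of relatedness, and no blinded review of that judgement is described. An investigator who knows that a patient takes two RAS blockers may attribute a raised potassium to treatment more readily than one whose patient takes a single agent. The reverse is also possible. A count that passes through this judgement could show a difference where none exists, or hide one that does. The judgement is also unnecessary, because potassium and creatinine are measured in everyone anyway.

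**Working it through.** The Protocol states no safety rate, safety sample size or safety test, so there is no figure of its own to reproduce. The check is mainly a comparison of texts.

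**Step 1. By which routes can an abnormality enter the safety variables?**

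- *Route (a), as an adverse event.* No relatedness filter applies. The definition allows a laboratory finding to be an adverse event. Collection, however, is described for events that patients volunteer or mention when asked. A patient does not report an asymptomatic high potassium, so its entry by this route rests on the investigator choosing to record it.
- *Route (b), as a clinical or laboratory abnormality.* It enters only if possibly related to the study drugs.

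If (a) already caught every abnormality, (b) would add nothing. Read as adding something, (b) brings in abnormalities not recorded as adverse events, but only those judged related.

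**Step 2. Which harms are exposed?**

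| Item | Entry without attribution | Exposed to the filter |
|---|---|---|
| Serious adverse events | Yes, reported whatever the attribution | No |
| Recorded non-serious adverse events | Yes | No |
| Serum creatinine | Yes, as a secondary outcome | Only as a counted abnormality (acute deterioration) |
| Potassium not recorded as an adverse event | Values recorded for safety analyses, but in no listed outcome | Yes |
| Other abnormalities not recorded as adverse events | Data recorded for safety analyses | Yes |

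**Step 3. Is there an attribution-free count of hyperkalemia elsewhere?** A potassium value of 5.5 mEq/L appears in the exclusion criteria and in the back-titration rule of Study Design and Treatment. Both uses are conditional on diuretic therapy and on optimised metabolic and acid/base control. Neither defines a safety outcome.

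**Step 4. Illustration under assumed inputs.** This applies only to a count restricted to attributed cases. Take 188 patients per arm (Sample Size section), the same true rate r in both arms, and attribution probabilities d (dual) and s (single).

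- Counted cases: 188 × r × d and 188 × r × s.
- Apparent risk ratio: (r × d)/(r × s) = d/s.
- False-positive rate: the probability that a two-sided 5% two-proportion z test on the counted cases rejects, from exact binomial probabilities.

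| r (assumed) | d, s (assumed) | Counted cases | Apparent risk ratio | False-positive rate |
|---|---|---|---|---|
| 5% | 90%, 60% | 8.5 vs 5.6 | 1.50 | 11.6% |
| 5% | 95%, 75% | 8.9 vs 7.1 | 1.27 | 7.5% |
| 8% | 90%, 60% | 13.5 vs 9.0 | 1.50 | 16.1% |
| 8% | 95%, 75% | 14.3 vs 11.3 | 1.27 | 9.4% |
| 12% | 90%, 60% | 20.3 vs 13.5 | 1.50 | 22.9% |
| 12% | 95%, 75% | 21.4 vs 16.9 | 1.27 | 11.9% |

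With equal attribution (90% in both arms) the ratio is 1.00 and the false-positive rate stays near 5%. In the other direction, true rates of 12% (dual) and 8% (single) with attribution of 60% and 90% give 0.12 × 0.60 = 0.072 and 0.08 × 0.90 = 0.072. The counted rates are then equal and the excess disappears.

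**The case against.** A reader might infer that the whole hyperkalemia and renal comparison depends on an unblinded investigator's attribution. The documents do not support that, for these reasons:

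- The same sentence counts all adverse events first, without a filter. Its verb is to include, which is not exclusive.
- Laboratory findings can be adverse events whether or not they are related, and serious events are reported regardless of attribution.
- All laboratory parameters are recorded for safety analyses, and nothing restricts those analyses to attributed values.
- Laboratory staff are blinded, and serum creatinine is compared as a secondary outcome in its own right.

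All of this stands and sets the limit of the point. It does not remove it. Study Design and Treatment says what is recorded, while Safety variables says what counts, and the two differ. Blinding in the laboratory protects the measurement but not the attribution.

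Two further objections deserve weight. First, the parenthesis in the Safety variables sentence may only name types of abnormality that these drugs can cause, and no section says that the case-by-case causality rating decides what counts. That reading is possible, which is a reason to settle the wording. Second, tabulation of laboratory data usually belongs in a statistical analysis plan, which is not shown here. That is fair for table layouts, but the condition is stated in the Protocol and conflicts with the Protocol's own text.

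It is also right that the Protocol specifies no safety test, so the error rates in the illustration do not describe any planned analysis.

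**Conclusion.** The point holds in a limited form. The Safety variables section places a relatedness condition on the named clinical and laboratory abnormalities, in an open-label trial where the investigator rates causality. This disagrees with Study Design and Treatment and with the adverse event definition. The comparison between arms is partly exposed: chiefly potassium, and other abnormalities that are not recorded as adverse events. The renal comparison is better protected, through serum creatinine as a secondary outcome.

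The size of any bias cannot be derived from the documents. The risk ratio of 1.5 and the false-positive rate of about 16% follow from an assumed true rate of 8%, assumed attribution of 90% and 60%, and a count restricted to attributed cases. They show what such a filter could do and are not estimates for this trial. The conclusion rests on reading the relatedness condition as applying case by case, which is the natural reading but not the only one. This is a free improvement; it does not show that the safety comparison is biased.

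**What to change.** 1. In Safety variables, delete the closing relatedness condition (the last six words of the sentence), so that the section agrees with Study Design and Treatment and with the adverse event definition.
2. State that potassium and creatinine abnormalities are compared by arm from the measured values of all randomised patients at the scheduled visits in Appendix 1, whatever the investigator's attribution.
3. Set the cut-offs for these counts in advance, for counting only, and keep them separate from the back-titration rule in Study Design and Treatment, which carries clinical conditions of its own. No change to patient management is implied.
4. Show values from the extra visits separately. They should not be lost, but their number may differ between arms because care is open label.
5. Keep investigator-judged relatedness as a descriptive addition.

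The cost is a short change to the Protocol text and one additional table. No new data, visits or staff are needed.

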### **SAMPLE SIZE**

Primary efficacy comparison will be between combined ACE inhibitor plus ARB therapy and ACE inhibitor alone. On the basis of the outcome data of the BENEDICT study (14) and the first interim analysis 6% of patients with high normal albuminuria are expected to progress to microalbuminuria every year. It is predicted that at the time the last randomized patient will have completed the planned 3-year treatment period (study end), the median follow-up of the whole study group will approximate 4.5 years. Thus, assuming a 6% yearly incidence of microalbuminuria and a 4.5-year follow-up, 27% of patients in the ACE inhibitor group are predicted to develop microalbuminuria throughout the study period. Similar figures are expected for patients in the ARB group. On the basis of preliminary evidence in type 2 diabetes (10) this figure is, conservatively, predicted to decrease by 45% (from 27% to 14.85%) by combined therapy. To give the trial an 80% power to detect by a two-side test with a type 1 error of 5% the expected reduction in microalbuminuria events, 179 patients per group should complete the study. Thus, to account for a 5% drop-out rate, 188 patients per group should be included for a total of 564 patients. Assuming a similar incidence of events in the ACE inhibitor and ARB groups, this sample size should provide adequate power to detect a difference, if any, also between the combined and the ARB inhibitor treatment group. Comparative analyses will consider also the ACE inhibitor and the ARB arms. No sample size, however, is calculated for this comparison.

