Statistical analysis will be performed according to the intention-to-treat principle. Statisticians and investigators involved in statistical analyses will be blinded to the treatment assignments of the subjects. Primary end point is time to progression to microalbuminuria. At variance with end points such as ‘death’ or ‘dialysis’, the microalbuminuric state does not allow a clear cut recognition of the exact occurrence date, but, rather, two dates can be identified: the last time the patient is found to be normoalbuminuric and the first time the patient is detected as microalbuminuric. This kind of end point gives rise to interval censored data. The interval censoring method will take into account that the ‘true’ date of microalbuminuria development lies within this interval. The primary analysis will be performed by means of the accelerated failure time model, implemented in SAS PROC LIFEREG, which allows direct incorporation of interval censored data, and by use of proportional hazards model, implemented in SAS PROC PHREG. The following baseline covariates will be included in the model: site, age, gender, smoking habits (never vs. current and former), a measure of blood pressure and log transformed urinary albumin excretion. Kaplan-Meier curves will also be plotted, using the midpoint of the interval as event time. One interim analysis will be undertaken on the intention-to-treat population, when about 50% of total information is expected to be collected. The method of O’Brien and Fleming will be used to determine for statistical significance at the interim evaluation, that would constitute grounds to recommend trial termination. This threshold will be a P value of 0.0054 (nominal significance level) or less in order to ‘preserve’ an overall 5% level of significance. A further evaluation will take place at the end of the enrolment period for the purposes of possible adaptation of the sample size or observation period in order to achieve adequate power. Other details regarding the statistical approaches will be supplemented by a detailed plan which will be prepared after release of the protocol but before the start of the clinical part of the study. Should new evidence come to light as a result of running other trials before this trial is analyzed or should new methods of analysis become available in the statistical literature, or should the trial be affected by unforeseen circumstances, it may be necessary to modify the analysis plan.

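### The 27% control incidence is 6% multiplied by 4.5 years; a 6% yearly incidence among patients still at risk gives about 24%, and 179 completers per group then have about 73–76% power rather than 80%

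*Protocol*

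**What the plan says.** All the planning figures are in the protocol's Sample Size section.

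- Event rate: "6% of patients with high normal albuminuria are expected to progress to microalbuminuria every year". The stated sources are the outcome data of an earlier prevention trial and the first interim analysis; the derivation is not shown.
- Follow-up: "the median follow-up of the whole study group will approximate 4.5 years" at study end.
- Control incidence: "assuming a 6% yearly incidence of microalbuminuria and a 4.5-year follow-up, 27% of patients in the ACE inhibitor group are predicted to develop microalbuminuria". Similar figures are expected in the ARB arm.
- Effect: this incidence is "predicted to decrease by 45% (from 27% to 14.85%) by combined therapy".
- Size, for 80% power at a two-sided 5% level: "179 patients per group should complete the study", and "to account for a 5% drop-out rate, 188 patients per group should be included for a total of 564 patients".

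The Statistical Analysis section adds that "Primary end point is time to progression to microalbuminuria", analysed by accelerated failure time and proportional hazards models. It also provides for a further evaluation when enrolment ends, at which the sample size or the length of observation may be changed to secure power. Under Main Outcomes, a patient whose microalbuminuria is confirmed has reached the endpoint, so each patient can contribute one event at most.

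**The concern.** Adding 6% for each year treats the whole starting group as still at risk throughout. For a once-only event it is not: patients who progress in year 1 cannot progress in year 2. The product rate × time approximates cumulative incidence well only when it is small, and at 0.27 it overstates it by about 3 percentage points.

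The 27% and the 14.85% derived from it are the two proportions behind the 179 per group. If both are too high, fewer events accrue than planned, and the primary comparison (combination versus benazepril) falls short of its stated power even when every planning assumption comes true. The uncorrected 27% would also be a misleading benchmark at the end-of-enrolment evaluation: a 6% rate running exactly as assumed would look like a shortfall in events.

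**Working it through.** **Inputs (protocol, Sample Size):** 6% per year; 4.5 years; 45% reduction applied to cumulative incidence; two-sided 5%; 80% power; 179 completers per group.

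**1. Reproduce the stated size.** Freedman's log-rank formula uses HR = ln(1 − p₂)/ln(1 − p₁), required events d = (1.960 + 0.842)² × [(1 + HR)/(1 − HR)]², and n per group = d/(p₁ + p₂).
- p₁ = 0.27 and p₂ = 0.1485 give HR = 0.511, d = 74.9 and n = 74.9/0.4185 = 178.9, that is, the stated 179.
- The pooled two-proportion formula gives 175 per group, and 80.9% power at 179.

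The size formula is therefore sound. What needs checking is the 27% put into it.

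**2. Check the 27%.** 6% × 4.5 = 27% exactly. Among patients still at risk:
- yearly risk of 6%: 1 − 0.94^4.5 = 24.3%
- constant hazard of 0.06: 1 − exp(−0.06 × 4.5) = 23.7%

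Conversely, 27% at 4.5 years needs a hazard of −ln(0.73)/4.5 = 7.0% per year, not 6%.

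**3. Power at 179 per group, 45% reduction kept.** Freedman power is Φ(√events × (1 − HR)/(1 + HR) − 1.960), with events = 179 × (p₁ + p₂).

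| Control vs combination | Events expected, two primary arms | Power, Freedman | Power, two proportions | Events required for 80% | n per group for 80% (Freedman; two proportions) |
|---|---|---|---|---|---|
| 27% vs 14.85% (stated) | 74.9 | 80.0% | 80.9% | 74.9 | 179; 175 |
| 24.3% vs 13.4% | 67.4 | 74.7% | 75.6% | 76.7 | 204; 200 |
| 23.7% vs 13.0% | 65.7 | 73.4% | 74.2% | 77.2 | 210; 207 |

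**4. Sensitivity.**
- *Spread of follow-up.* The protocol gives a 3-year minimum and a predicted median. If follow-up is assumed uniform from 3 to 6 years, average incidence is 23.6–24.2% and two-proportion power 74–75%.
- *Crude annualised 6%.* The Background section reports 86 of 441 (19.5%) progressing in the earlier trial. If the 6% is 19.5%/3.25 years (the 3.25 years is an assumption), the constant hazard is −ln(0.805)/3.25 = 0.0667. Incidence at 4.5 years is then 1 − exp(−0.300) = 25.9%, against 14.3% on the combination, and power is 78% (Freedman) or 79% (two proportions).
- *All 188 enrolled per group followed in full.* Power is 75–78% in the two corrected rows.

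**5. Follow-up at which 6% per year does give 27%.** ln(0.73)/ln(0.94) = 5.1 years (yearly risk), or −ln(0.73)/0.06 = 5.2 years (constant hazard). That is about 7 to 9 months beyond 4.5 years.

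**The case against.** **The meaning of 6%.** The protocol does not say whether the denominator is the starting group or the patients still at risk. If 6% of the starting group progressed each year, 27% would stand. Under the crude annualised reading the gap is about 2 points, and if all 188 per group were followed in full it would close (80.0%, Freedman). This part stands: the documents cannot settle the derivation, so a flat statement that power is 73–76% would claim too much. But the section itself uses the term yearly incidence, whose usual meaning refers to patients at risk and suits a time-to-event endpoint. A constant number of events from a shrinking risk set would also imply a rising hazard, which the protocol neither states nor justifies.

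**The planned re-evaluation.** The end-of-enrolment evaluation could absorb a shortfall of this size. That also stands, and it limits the harm. It does not correct the stated 27% or the power attached to it.

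**Readings that go too far.** A reader might apply the 45% to the hazard and obtain 66–68% power. The protocol does not support this: it takes the 45% off the cumulative figure explicitly, from 27% to 14.85%. A reader might also use the 40% difference in the Synopsis and obtain 62–64%. The disagreement between 40% and 45% is a separate matter and should not enlarge this one.

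**Conclusion.** The point holds as a correction to a planning figure. A 6% yearly incidence among patients at risk gives 23.7–24.3% at 4.5 years, and 179 completers per group then have about 73–76% power, some 4 to 7 points below the stated 80%. About 66–67 events are expected in the two primary arms, against about 77 required.

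This rests on three assumptions: the 6% refers to patients still at risk; 4.5 years can stand for everyone's follow-up; and the 45% reduction in cumulative incidence also holds at the lower base. If the 6% is a crude annualised proportion, power is about 78%. It would be wrong to infer that the sample-size formula is faulty, since it reproduces 179. It would also be wrong to infer that the trial cannot reach 80%, since the protocol already has a means of extending observation.

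**What to change.** In the Sample Size section:

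1. State how the 6% was derived: numerator, denominator and person-time or follow-up, from the earlier trial and from the interim data.
2. Unless that derivation supports another figure, replace 27% and 14.85% by about 24% and 13%.
3. Restate power as about 74% for 179 completers per group, with about 66–67 events expected in the two primary arms against about 77 required for 80%.

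If 80% is to be kept without more patients, use the observation-period adaptation already in the Statistical Analysis section. A median follow-up of about 5.1–5.2 years restores 27% at 6% per year. Guide that decision by events pooled over all three arms, because a count limited to the two primary arms would require the valsartan patients to be identified and would not be blinded.

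With the protocol's expectation that the ARB arm behaves like the ACE inhibitor arm, and 179 per group, the pooled count would be:
- at 4.5 years, 179 × (2 × 0.243 + 0.134) ≈ 111, or 179 × (2 × 0.237 + 0.130) ≈ 108 under constant hazard;
- at the extended follow-up, 179 × (2 × 0.27 + 0.1485) ≈ 123, if the 45% reduction still holds then.

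The cost is a few restated figures and, optionally, some 7 to 9 months of further observation under an existing provision. Keeping 80% by enrolment instead would take 200–210 completers per group rather than 179.

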### ***Secondary***

- To evaluate whether, at comparable blood pressure control, dual RAS blockade with combined therapy with halved doses of benazepril (10 mg/day) and valsartan (160 mg/day) reduces the incidence of microalbuminuria more effectively than valsartan (320 mg/day) given alone in high-risk patients with type 2 diabetes, hypertension and high normal albuminuria.
- To evaluate whether, at comparable blood pressure control, the effects of benazepril and valsartan therapy are similar or whether, alternatively, one of the two treatments offer a superior protective effect against the development of microalbuminuria in the above study population.
- To evaluate the effects of the three study treatments on the incidence of fatal and non-fatal cardiovascular events, regression to low-normal albuminuria (urinary albumin excretion  $<7\mu\text{g/min}$ ), albuminuria (considered as a continuous variable), serum creatinine, lipid profile, and GFR (in a representative subgroup);
- To assess the relationships, in the study group as a whole and within each treatment group, between renal outcome variables (including microalbuminuria and time-dependent changes in albuminuria) and fatal and non-fatal cardiovascular events, between achieved blood pressure or metabolic control and

renal and/or cardiovascular outcome variables and between achieved albuminuria reduction or residual follow-up albuminuria and renal and/or cardiovascular outcome variables.

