### **STATISTICAL ANALYSIS**

The main treatment group comparison is between dual RAS blockade with combined therapy with halved doses of benazepril (10 mg/day) and valsartan (160 mg/day) vs full doses of benazepril (20 mg/day), and the 5% level of significance in a two-sided test will be used for this comparison. Secondary comparisons will be a. combined therapy vs full doses of valsartan (320 mg/day) and b. full doses of benazepril (20 mg/day) vs full

doses of valsartan (320 mg/day). These descriptive comparisons will be according to a two-sided test and conducted at the 2.5% level of significance (two-sided test) to take account of multiple testing.

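### The claim of adequate power for combination versus valsartan ignores the 2.5% level set for that test (power is about 71%, not 80%), and the aim of finding benazepril and valsartan similar has only a difference test behind it

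*Protocol*

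**What the plan says.** The Sample Size section of the Protocol sizes one comparison, combination versus benazepril, at 80% power and a two-sided type 1 error of 5%. It assumes that "27% of patients in the ACE inhibitor group are predicted to develop microalbuminuria throughout the study period" and that combined therapy lowers this by 45%, to 14.85%. This leads to 179 completers per group, raised to 188 for drop-out, 564 in all. For valsartan it adds "Similar figures are expected for patients in the ARB group", and from this alone concludes that "this sample size should provide adequate power to detect a difference, if any, also between the combined and the ARB inhibitor treatment group". For benazepril versus valsartan it says "No sample size, however, is calculated for this comparison".

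The Statistical Analysis section sets different levels. For combination versus benazepril, "the 5% level of significance in a two-sided test will be used for this comparison". The two secondary comparisons (combination versus valsartan, and benazepril versus valsartan) are called descriptive and are "conducted at the 2.5% level of significance (two-sided test) to take account of multiple testing".

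The secondary aims ask whether "the effects of benazepril and valsartan therapy are similar or whether, alternatively, one of the two treatments offer a superior protective effect". The Synopsis, under Expected Results, anticipates a similar effect of the two drugs on microalbuminuria. The Protocol states no equivalence or non-inferiority margin.

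**The concern.** There are two mismatches, both between statements that the Protocol itself fixes.

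**Power statement and test level.** Equal event rates carry the power of the first comparison over to the second only if the significance level is also the same. Here it is halved. The sentence gives no figure, but it rests on the 80% calculation, and 80% is the only power standard in the Protocol (Synopsis and Sample Size). A reader will take it to mean about 80% and will underestimate the chance of missing a real advantage of the combination over valsartan.

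**Question and test.** A two-sided difference test can support the conclusion that one drug is better. It cannot support the conclusion that they are similar, because non-significance is also what a small or imprecise comparison produces. The aim sets out two possible answers, similar or one superior, and the analysis can deliver only the second. The Background presents this comparison as a reason for the trial, linking it to the replacement of ACE inhibitors by costlier ARBs. An unsupported finding of similarity would therefore carry weight.

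**Working it through.** **Inputs (Protocol).** Incidence 27% on benazepril, taken as 27% on valsartan as well; 14.85% on combination; 179 completers and 188 randomized per group; two-sided 5% for the primary and 2.5% for each secondary comparison (Sample Size and Statistical Analysis). The endpoint is time to event.

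**Step 1: reproduce the planned size (Freedman log-rank formula).**
- Hazard ratio: ln(1 − 0.1485) / ln(1 − 0.27) = 0.511.
- k = (1 − 0.511) / (1 + 0.511) = 0.324.
- Events: (1.960 + 0.842)² / k² = 74.9.
- Per group: 74.9 / (0.27 + 0.1485) = 178.9, so 179. This matches the Protocol exactly.

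**Step 2: power for combination versus valsartan.** Expected events are 179 × 0.4185 = 74.9. Power = Φ(√events × k − z), with √74.9 × 0.324 = 2.80.
- Two-sided 5%: Φ(2.80 − 1.96) = 80.0%.
- Two-sided 2.5%: Φ(2.80 − 2.24) = 71.3%.
- All 188 per group evaluable (78.7 events), two-sided 2.5%: 73.6%.

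**Step 3: other formulas at two-sided 2.5%.**

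| Method | 179 per group | 188 per group |
|---|---|---|
| Freedman log-rank | 71.3% | 73.6% |
| Two proportions, pooled | 72.3% | 74.6% |
| Two proportions, continuity-corrected | 67.7% | 70.3% |
| Schoenfeld log-rank | 74.7% | 77.0% |

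None reaches 80%. For 80% at 2.5%, the Freedman formula needs (2.241 + 0.842)² / k² = 90.7 events, or 90.7 / 0.4185 = 216.6, about 217 completers per group. The pooled two-proportion formula needs 212.

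The result depends on the 45% reduction. With the 40% difference named in the Synopsis (27% to 16.2%), power at 2.5% with 179 per group is about 59% (Freedman) or 60% (pooled two-proportion).

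**Step 4: precision of benazepril versus valsartan.** With 27% in both arms, expected events are 2 × 0.27 × 179 = 96.7. The standard error of the log hazard ratio is about 2 / √96.7 = 0.203. For an observed hazard ratio of 1:
- 95% interval: exp(±1.960 × 0.203), about 0.67 to 1.49.
- 97.5% interval: exp(±2.241 × 0.203), about 0.63 to 1.58.
- On the risk-difference scale, the 97.5% half-width is 2.241 × √(2 × 0.27 × 0.73 / 179) = 10.5 percentage points.

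Even identical observed incidence would leave hazard differences of more than a third in either direction compatible with the data.

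**The case against.** The strongest reply is about weight. The Protocol says only that power is adequate, gives no figure and does not claim the same power as for the primary comparison. Analysis is by intention to treat with 188 randomized per group, so 179 may be slightly pessimistic. A power in the low to middle seventies is not unusual for a comparison labelled secondary and descriptive. The Protocol also plans an evaluation at the end of enrolment that may adapt sample size or observation period to secure power, and leaves further statistical detail to a separate plan.

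Much of this stands. The loss is about 9 points, and a reader who inferred that the trial cannot answer its secondary questions would go further than the documents allow. What does not fall away is the mismatch itself: the power sentence and the 2.5% level are both fixed in the Protocol. The figure of 188 is an upper bound, since drop-outs contribute only part of their follow-up, and it still gives less than 80%. The end-of-enrolment evaluation does not say which comparison it protects.

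On similarity, a reader might infer that the Protocol will treat a non-significant result as proof that the drugs are alike. No passage states that rule. The aim is an open question, the Synopsis text is an expectation, and the Protocol says openly that the comparison was not sized. What remains is that the word similar appears in an aim without any criterion.

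A reader might also infer that the 5%, 2.5% and 2.5% levels leave the overall error rate uncontrolled. That is not supported either. Separating one main comparison from two descriptive ones that share 5% between them is an accepted convention.

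**Conclusion.** The point holds as a misstatement of power and a gap between one aim and its analysis. It does not show a failed design.

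For combination versus valsartan, power at the stated 2.5% level is about 71% with 179 completers per group and about 74% if all 188 are evaluable. This assumes 27% incidence on valsartan, a 45% reduction with combination, and the formula that reproduces the planned size. The chance of missing an effect of that size is about 29%, against the 20% a reader would assume.

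For benazepril versus valsartan, the stated test cannot establish similarity, and an expected 97.5% interval of about 0.63 to 1.58 is too wide for non-significance to be informative. That interval assumes 27% incidence in both arms and about 97 events.

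The primary comparison and its sample size are unaffected.

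**What to change.** 1. **Sample Size section.** Replace the statement of adequate power for combination versus valsartan with one giving the figure and the level: about 71% power at the two-sided 2.5% level, assuming 27% versus 14.85% and 179 completers per group.
2. **Secondary aims and Statistical Analysis section.** State that benazepril versus valsartan will be reported as a hazard ratio with its confidence interval, and that a non-significant difference will not be interpreted as similarity. Giving the expected 97.5% interval (about 0.63 to 1.58 with 27% in both arms) would show readers the precision available.

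Both are wording changes. They need no additional patients or data and leave the significance levels as they are. The cost is a less favourable stated power for one secondary comparison and a narrower conclusion for the other.
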